**Nature and extent of the burden and risks associated with participation, benefit and group relatedness:** The burden is expected to be minimal as it will only entail additional blood draws, which will be taken from clinical lines or in addition to pricks for clinical purpose. The long-term follow up will be held as part of already organised follow-up outdoor clinics and which are developed to help children and their parents to recover physically, emotionally and socially after ICU admissions. For mechanistic and exploratory studies, muscle strength testing and an ultrasound evaluation of the skeletal muscle and adipose tissue compartments will be performed. Furthermore, as far as practically feasible, every patient is approached just prior to hospital discharge, to complete a validated, semi-structured child health questionnaire (Functional Independence Measure (WEEFIM), Health Utilities Index (HUI) and Child Health Questionnaire (CHQ)).

The risk in participating to the study and being randomized to the "late PN" group are negligible, and specifically compass an increased risk of developing hypoglycemia and/or underfeeding. However, safety measures will be taken to further decrease these risks.

**GROUP relatedness:** This study was already performed in adult ICU patients. However, the results of this study should NOT be translated one-on-one to the pediatric patient, as critically ill children of different age groups have different metabolic and nutritional issues. Therefore, this study deserves to be repeated in our population of critically ill children.

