### **15.4 Sample size calculation**

The sample size (N=1440, 720 per arm) is calculated in order to detect, with at least 80% power (one-tailed; the two-tailed power is 70%) and 95% certainty, a reduction in PICU infections from 20% to 15% and, with at least 90% power (two-tailed) and 95% certainty, a reduction in mean duration of stay in PICU of 1 day. With this sample size, and for safety reasons, also any substantial impact on mortality (increase or decrease with an absolute +/- 2%, although unexpected taken the adult data), can be excluded with a power of around 62-75% depending on the true mortality in the total population. We plan to calculate the true power of the study for detection of any eventual smaller differences in these outcomes.

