### ***Blood glucose management***

Blood glucose management will be performed as through standard practice in all participating centers. (for protocols see the appendices)

In **Leuven**, patients in both study groups receive continuous insulin infusion to target blood glucose levels of 50-80 mg/dl when aged < 1y and 70-100 mg/dl when aged ≥ 1 year. Blood glucose and potassium are monitored systematically every 1 – 4 hours on the blood gas analyser (ABL Radiometer®, Copenhagen, Denmark) using arterial blood samples. (14)

In **Rotterdam**, patients in all age groups receive continuous insulin infusion to target blood glucose levels of 72-145 mg/dl, except for patients with traumatic brain injury (108-145 mg/dl), using a step-wise nurse driven glucose control protocol. Blood glucose and potassium are monitored systematically every 1 – 3 hours on the blood gas analyser (ABL 625; Radiometer®, Copenhagen, Denmark) using arterial blood samples. (15)

In **Edmonton** patients in all age groups receive continuous insulin infusion to target blood glucose levels <180 mg/dl

[figure not shown]

Nutritional protocol showing schematic decision tree

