Unpublished data obtained in a rabbit model of prolonged critical illness suggest that relative fasting during critical illness reduces (peripheral) activation of the somatotrophic and thyrotrophic axes with lower levels of insulin-like growth factor-I (IGF-I) and triiodothyronine (T3) levels, but also attenuates the rise in the stress hormone cortisol as compared with moderate dose intravenous feeding during critical illness. These findings urge a thorough analysis of the impact of early versus late PN on these neuroendocrine axes in the critically ill children included in our study. We hypothesize that late PN results in suppression of the neuroendocrine axes, in concert with the intensive insulin therapy. Unlike conventional belief, we also hypothesize that such suppressed neuroendocrine axes during prolonged critical illness could be associated with a beneficial acute and long-term clinical outcome.

We will evaluate the activation of the somatotrophic axis in the acute and chronic phase of critical illness by measuring the levels of growth hormone (GH), acid-labile subunit (ALS), IGF-I and its binding proteins (IGFBP-1 and IGFBP-3), the activation of the thyrotrophic axis by analysis of thyroxine (T4), T3, reverse T3 (rT3) and thyroid stimulating hormone (TSH), and the adrenal axis by adrenocorticotrophic hormone (ACTH) and cortisol. The metabolism of cortisol will be studied further by the relative levels of its metabolites excreted in urine (26) and by collecting hair samples for the long term cortisol levels. The impact of early versus late PN on the neuroendocrine axes will be studied in relation to markers of catabolism, muscle volume and strength, as well as clinical outcome. The clinical outcome will be assessed during follow-up consultations that are held in the departments that have referred their patients to the ICU in Leuven and Rotterdam.

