### ***General rules of the statistical analysis***

All analyses will be done on intention to treat basis. The analyses will be performed on the whole set of patients and by subgroups of patients based on the primary diagnostic categories used as prognostic factors for stratification and on septic/non-septic groups of patients.

A consort diagram will be reported. The data file will be finalised 90 days after inclusion of the last patient. To assess compliance with the study protocol, the amounts of PN and EN actually given in the two study groups during the intervention window of 7 days will be reported as absolute numbers and percentages of target calories. Discrete variables will be summarised by frequencies and percentages and analysed by (exact) Chi- square test or logistic regression analysis. Continuous variables will be summarised by use of either mean or standard deviations (SD) or median and interquartile range as appropriate and compared using Student's t-test or Mann-Whitney-U test, as appropriate. Time to event analysis will be performed by Cox proportional hazard analysis. All outcomes will be analysed in an uncorrected manner as well as (jointly) corrected for risk factors (type and severity of illness, age, on admission nutritional status and risk scores). *A priori* defined subgroup analyses will be performed for patients admitted to ICU after cardiac surgery as compared with all other patients; for patients with and without sepsis upon admission; for patients with contra-indications for EN on admission or not. For all endpoints, differences will be considered statistically significant whenever the p-value is lower than 0.05 without correction for multiple testing.

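### No centre-specific or age-specific treatment effect is planned, although the three centres control glucose very differently and the trial enrols ages 0 to 18

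*Supplement*

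**What the plan says.** **Glucose control (final protocol, 16.1).** In Leuven, "patients in both study groups receive continuous insulin infusion to target blood glucose levels of 50-80 mg/dl when aged < 1y", and to 70-100 mg/dl from 1 year. In Rotterdam the target is 72-145 mg/dl (108-145 in traumatic brain injury). In Edmonton, "patients in all age groups receive continuous insulin infusion to target blood glucose levels <180 mg/dl".

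**Randomisation.** The Summary and Study Design sections state that it is done per centre, in blocks within diagnostic stratum.

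**Subgroups.** Section 20.1 names the diagnostic strata, septic versus non-septic patients, patients with and without contra-indications to enteral feeding, and states that "subgroup analyses will be performed for patients admitted to ICU after cardiac surgery as compared with all other patients". Sections 20.3 and 20.4 repeat parts of this list. Centre and age appear in none of them.

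**Adjustment.** Section 20.1 corrects for type and severity of illness, age, nutritional status and risk scores. Centre is absent. On error control: "differences will be considered statistically significant whenever the p-value is lower than 0.05 without correction for multiple testing".

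**SAP.** It covers a secondary analysis of undernourished children. Centre and age are adjustment factors there, and neither is named as an effect modifier.

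**Sample size (15.4).** "The sample size (N=1440, 720 per arm") is set to detect, "with at least 80% power (one-tailed; the two-tailed power is 70%) and 95% certainty, a reduction in PICU infections from 20% to 15" per cent.

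**The concern.** The trial is meant to supply evidence for practice guidelines (Introduction), so readers elsewhere will ask whether the result holds under their own glucose practice and age mix. A pooled estimate cannot answer that. Adjusting for age, or for centre, gives one average effect; it does not examine whether the effect varies.

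The safety comparison makes this concrete. Section 18.1.3 counts patients below 40 mg/dl and regards those without early PN as possibly at greater risk. The lower limit of the glucose target is 50 mg/dl for Leuven infants, 70 for older Leuven children and 72 in Rotterdam, and no lower limit is stated for Edmonton. The background risk may thus depend on centre and age, and one count per arm would not show whether an excess arose under a single regime.

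An unplanned centre analysis would remain possible after the fact. It would carry less weight because it would have been chosen once the data were known, in a plan that already runs many uncorrected comparisons.

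**Working it through.** **1. The plan's own figure.** Inputs from 15.4: n = 720 per arm, p1 = 0.20, p2 = 0.15, so d = 0.05 and p̄ = 0.175.

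Power = Φ{[d − z·√(2p̄(1−p̄)/n)] / √[(p1q1 + p2q2)/n]}

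- √(2 × 0.175 × 0.825/720) = 0.02003
- √[(0.16 + 0.1275)/720] = 0.01998
- Two-sided: (0.05 − 1.96 × 0.02003)/0.01998 = 0.54, power 70%
- One-sided: (0.05 − 1.645 × 0.02003)/0.01998 = 0.85, power 80%

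Both agree with 15.4.

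**2. What pooling can hide.** The protocol gives no planned number of patients per centre, so the shares below are assumptions. Control risk is taken as 20% at every centre. If centres holding a share s have no effect and the rest have 5 points, the pooled difference is 5(1 − s) points.

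| Share without effect | Pooled difference (points) | Two-sided power |
|---|---|---|
| 5% | 4.75 | 66% |
| 10% | 4.5 | 61% |
| 20% | 4.0 | 51% |
| one third | 3.3 | 37% |
| two thirds | 1.7 | 12% |

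Conversely, a pooled 5 points could be 10 points in half the patients and none in the rest (0.5 × 10 + 0.5 × 0). None of the listed subgroups would test this directly.

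**3. Precision of one centre's estimate.** With 720s patients per arm, the 95% half-width is 1.96 × √[(p1q1 + p2q2)/(720s)]. The range below runs from 20% v 15% (numerator 0.2875) to 20% v 20% (numerator 0.32).

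| Share s | n per arm | Half-width (points) |
|---|---|---|
| one third | 240 | 6.8 to 7.2 |
| 20% | 144 | 8.8 to 9.2 |
| 10% | 72 | 12.4 to 13.1 |
| 5% | 36 | 17.5 to 18.5 |

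**4. Power of the arm-by-centre test** (2 df, alpha 0.05, risk-difference scale). Suppose one centre has no effect and the other two share an effect d. Let w0 be the inverse variance of the difference at the first centre, and W the sum for the other two. The noncentrality is λ = d²·w0·W/(w0 + W).

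Equal thirds (w0 = 240/0.32 = 750):
- 0/5/5 points: W = 2 × 240/0.2875 = 1670; λ = 0.0025 × 750 × 1670/2420 = 1.29; power 16%
- 0/10/10 points: W = 2 × 240/0.25 = 1920; λ = 0.01 × 750 × 1920/2670 = 5.39; power 54%

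Centre without effect holding 10%, the others equal (w0 = 72/0.32 = 225):
- 0/5/5 points: W = 2 × 324/0.2875 = 2254; λ = 0.51; power 9%
- 0/10/10 points: W = 2 × 324/0.25 = 2592; λ = 2.07; power 23%

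The estimates with their intervals are therefore more useful than the interaction p-value.

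**The case against.** **A reader might infer that the protocol predicts these effect modifiers and then ignores them.** It does not.

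- *Age.* The remark in the Summary, "as critically ill children of different age groups have different metabolic and nutritional issues", explains why adult results should not be carried over to children. Section 21.4 makes the same contrast with adults. Neither says that the effect of late PN will differ between younger and older children.
- *Insulin.* The sentence "We hypothesize that late PN results in suppression of the neuroendocrine axes, in concert with the intensive insulin therapy" belongs to work package 3 and concerns hormone axes. The next sentence links suppressed axes to clinical outcome only as a possibility. No differing effect on infections or ICU stay is forecast.

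**A reader might also infer that an arm-by-centre analysis would show whether glucose control changes the effect.** It cannot. Centre also carries case mix (61% of Leuven admissions in 2010 followed cardiac surgery, 15.1) and PN products (16.1).

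**Internal validity is not threatened.** With randomisation per centre, both arms at a centre share one glucose regime, and all centres aim for the same energy and protein targets (16.1). This stands.

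**The remedy adds low-powered comparisons to a long uncorrected list.** This stands as a reason to label them supportive. It is not a reason to omit them, because they use the randomisation structure and data already recorded.

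**The size of the masking depends on unknown shares.** This also stands, especially as Edmonton joined by an amendment dated May 2013. The working therefore gives a range.

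**Conclusion.** The gap is real and minor. The final protocol has no centre-specific or age-specific estimate of the treatment effect for either primary endpoint or for hypoglycaemia below 40 mg/dl, and it leaves centre out of its adjustment set although randomisation is per centre. The SAP does not fill the gap for the main trial.

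The consequence is limited to what the result can be said to show: the pooled effect is a valid average, but its consistency across centres and ages would not be examined by plan. How much this could hide depends on centre shares that the documents do not give. For one centre without effect, pooled power for infections would be between 66% (share 5%) and 37% (share one third), assuming 20% control risk everywhere and 5 points elsewhere. No comparable figure was derived for ICU stay. The point makes no judgement on which glucose regime is appropriate.

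**What to change.** In 20.1, with 20.3 aligned, for new infections, time to discharge alive from ICU, and hypoglycaemia below 40 mg/dl:

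1. Add centre to the adjusted models.
2. Prespecify arm × centre, reporting the three centre-specific estimates with 95% intervals. For hypoglycaemia, also give counts by arm and centre.
3. Prespecify arm × age, with age continuous.
4. State the effect scale, and that these are supportive checks of consistency, not a test of glucose control.

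The cost is a few lines of text; centre and age are already recorded. State the downside too: the arm-by-centre test has about 16% power for 0/5/5 points and 54% for 0/10/10 with equal thirds, and less if one centre is small. Centre-specific limits would be about ±7 points at one third of patients, ±12 to 13 at 10%, and about ±18 at 5%.

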### Safety endpoints

Safety endpoints comprise vital status, hypoglycaemia, serious adverse events and complications related to the mode of nutrition. Survival up to 90 days after randomization in both treatment groups will be compared by Kaplan Meier survival plots. The impact of "late PN" versus "early PN" will be analyzed, with and without correction for risk factors, by Cox

proportional hazard analysis. In addition, we will record vital status at ICU and hospital discharge, and will analyze differences with Chi-square testing. As the randomized study intervention only takes place during a time window up to the 8th day in ICU, we also plan to analyze early lethality within this time window in the intention to treat population as part of the safety analysis.

## **20.2 Univariate analysis**

Discrete variables will be summarized by frequencies and percentages and analyzed by (exact) Chi-square test or logistic regression analysis. Continuous variables will be summarized by use of either mean or standard deviations (SD) or median and interquartile range as appropriate and compared using Student's t-test or (exact) Mann-Whitney-U test, as appropriate. Time to event analysis will be performed by Cox proportional hazard analysis. Time to discharge alive from ICU will be reported by Kaplan-Meier plots, with ICU non-survivors censored beyond the longest ICU stay of survivors and censoring time of patients still in the ICU at closing of the data file (90 days after last patient inclusion) over both treatment groups. The impact of "late PN" versus "early PN" will be analyzed, with and without correction for age, nutritional status and risk categories and type and severity of illness, by Cox proportional hazard analysis. The distribution of the actual time to discharge from ICU will be reported for ICU-survivors and ICU-non-survivors separately. In view of the time window of the randomized intervention in ICU, also the proportion of patients staying beyond 8 days in ICU will be reported.

## **20.3 Multivariate analysis**

All outcomes will be analyzed in an uncorrected manner as well as (jointly) corrected for risk factors (type and severity of illness, age, on admission nutritional status and risk scores). Another *a priori* defined subgroup analysis will be performed for patients admitted to ICU after cardiac surgery as compared with all other patients. Also an *a priori* subgroup analysis is planned for patients with and without sepsis upon admission.

All analyses will be performed uncorrected as well as corrected for age, nutritional status and risk categories and type and severity of illness. Time-to-event analysis will be analyzed similarly as the primary endpoint. Proportion of patients requiring support of vital organ functions and distribution of duration of support will be analyzed by non-parametric or parametric testing depending on the normality of the distribution in the subgroup of patients for which support was needed. Proportions will be compared using chi-square testing. Results of repeated measurements will be analyzed using an appropriate model for longitudinal data.

a. Time to final (alive) weaning from mechanical respiratory support: patients still on mechanical respiratory support at closing of the data file (90 days after last patient inclusion) will be censored at that time point. ICU non-survivors will be censored beyond the longest duration of mechanical respiratory support of the survivors.

b. Kidney failure: Proportion of patients in need for renal replacement therapy (RRT) during ICU stay; distribution of duration of RRT (for those patients requiring RRT); proportion of patients with a post-randomization diagnosis of new kidney injury/failure (defined by modified Risk, Injury, Failure, Loss, and End-stage Kidney (RIFLE) classification criteria as a plasma creatinine doubling or more during ICU stay) in both treatment groups. In addition, the duration of a score RIFLE $\geq$ 2 will be used as a marker of time to recovery of kidney damage.

c. Need for pharmacological or mechanical hemodynamic support during ICU stay, and duration of such need.

In addition, time to final (alive) weaning from all pharmacological or mechanical hemodynamic support in ICU will be analyzed, with ICU non-survivors censored beyond the longest duration of pharmacological or mechanical hemodynamic support of the survivors and censoring time of patients still on such support at closing of the data file (90 days after last patient inclusion) over both treatment groups.

d. Number of readmissions to the PICU.

e. Liver dysfunction: Proportion of patients during the time window of the intervention and during the whole ICU stay presenting with cholestatic or cytolytic liver dysfunction will be compared.

f. Inflammation: Effect of the intervention on inflammation will be analyzed by comparing the distribution of the highest value reached during ICU stay and changes from baseline to the highest value and by comparing time profiles of daily C-Reactive Protein values.

g. Child health questionnaire scores (WEEFIM, HUI, CHQ) at hospital discharge in both treatment groups will be compared.

#### **20.4 Interim analysis**

As the previous study in adults has shown that lethality was not different among the study groups and that morbidity was prevented by withholding feeding, and since the participating centers are currently providing early PN, repeated interim analyses for efficacy are not required. However, one formal “safety” interim analysis will be planned after patient number 720 has left the ICU, during which the independent DSMB will have access to un-blinded results on ICU mortality, hospital mortality and serious adverse events. The DSMB will then judge on whether or not to prematurely stop the clinical trial for safety reasons, or to perform more safety interim analyses. The DSMB will advise on eventual continuation of the study to completion, under monitoring of the serious adverse event. Because the primary efficacy endpoint will not be analyzed, no correction of the significance level at the final analysis will be necessary.

The safety analyses will be done on the whole set of patients and by subgroups of patients based on the primary diagnostic categories used as prognostic factors for stratification and on septic/non-septic groups of patients.

## **21. ETHICAL CONSIDERATIONS**

### **21.1 Regulation statement**

The study will be conducted in accordance to the protocol as described in the European Medicine Agency's "Note for guidance on good clinical practice CPMP/ICH/135/95" as well as the Declaration of Helsinki (*59th WMA General Assembly, Seoul, Korea, October 2008*) and in accordance with the Medical Research Involving Human Subjects Act (WMO).

### **21.2 Recruitment and consent**

The study protocol and consent forms will be sent for approval by the Institutional Review Board of the Katholieke Universiteit Leuven and the Erasmus MC (Lokale uitvoerbaarheid) and by the competent Belgian and Dutch authorities (CCMO). Written informed consent is obtained from the parents or the legal guardian by the investigator's team or one of the supervising doctors, who will inform the parents of the patients (and the patients themselves if the age is > 12 years) and ask for their consent. The parents / legal guardians and (if applicable) the patients will receive a patient information letter and an informed consent form.

Written informed consent will be obtained from the patient or the closest family member or legal guardian. For planned PICU admissions after elective procedures, informed consent will be asked beforehand, if possible.

For emergency PICU admissions, treatment allocation will be done after assessment of the patient for eligibility by the attending physician within the time frame of two hours. If eligible, the patient will be randomized into the study and the allocated glucose infusion (with micronutrients) will be started. Informed consent will be asked within the time frame of 24 hours (deferred informed consent) as a nutritional regimen has to be initiated already on admission. When consent is given, the allocated nutritional regimen will proceed (Early (with additional lipids and protein targeting nutritional goals < day3) vs Late (no PN)). When NO consent is given, the nutritional regimen and glucose infusion will be placed under responsibility of the supervising clinical team of doctors.

The parents or legal guardians can withdraw the patient from the study at any time, without penalty or impact on treatment.

